### Exercise

A gym orientation at the College of Kinesiology research gym facility will be provided to familiarize the participants with the aerobic equipment used during the supervised gym activity. The exercise-training laboratory is fully equipped with aerobic exercise machines and is reserved exclusively for research participants. Aerobic activity will be prescribed as part of the recommended “standard of care” and to reduce variability in this lifestyle factor between participants. Standard of care of exercise training and the TLC guidelines reduces variability among our participants. It is also a design which is ethically sound as it would not be ethical to include a control group that received no care because women with PCOS are a population that requires treatment.

Prior to the beginning of the intervention, the subjects’ current level of physical activity will be assessed via a validated Physical Activity Questionnaire [25]. Exercise training will involve aerobic training 5 days/week for 45 min/day with 3 required sessions in our physical activity facility in the College of Kinesiology at the University of Saskatchewan. This allows research assistants to monitor and support participants as well as address any issues encountered. Exercise will involve walking or training on elliptical machines, rowing machines or stationary bikes, depending on the individual participant’s preferences. Participants will be encouraged to exercise at an intensity of at least 60% of their age-predicted maximal heart rate (i.e., 220 minus age). Instruction will be provided by a research assistant on how to calculate and obtain heart rate measures. This amount of aerobic exercise is the minimal level of exercise shown to be beneficial for improving blood lipids [26].

### Diet

Women in the TLC group will be instructed to continue following the TLC diet prescribed during the lead-in phase. Women in the pulse group will be provided with two pulse meals per day and instructed to follow the TLC guidelines for breakfast and snacks. The pulse-based diet will include a variety of meals prepared with dry peas, lentils, chick peas and faba beans. Two standard meals will be supplied per day to participants (i.e., lunch, dinner) containing approximately 150 g per day of pulses dry weight (250 g per day wet weight). These quantities are based on amounts proven beneficial for lowering blood glucose and lipid levels [13, 27, 28]. The research team will be in contact with participants about food preferences and allergies and participants will have input into which meals are received out of the variety of meals including frozen and fresh options. Meals will be picked up weekly by participants at the exercise facility. Subjects will be counseled to replace foods normally eaten for lunch and supper with the pulse-based food so as not to increase daily caloric intakes.

### Compliance

Compliance to both diet and exercise will be monitored using a daily diet and exercise log book as well as a 1-day food record after every 4-weeks of following the intervention. All participants will be instructed to record daily exercise activity and duration. Women randomized to the pulse group will be required to log which pulse meals are consumed as well as the percentage consumed and both groups will be required to record whether the TLC guidelines are followed each day for all non-prescribed meals, which are all meals for TLC group.

#### Measurements

### Pulse consumption questionnaire

The pulse consumption questionnaire is a modified version of the validated DAILY (Diet Approaches to Increase Lentils in Youth) questionnaire and will be administered at enrollment (prior to TLC guideline counseling) to determine the beliefs and barriers to the consumption of pulses in this population, as well as their current intake of pulses in their diet [29]. The DAILY questionnaire was developed by our research group and has been used in diverse populations.

### Quality of life questionnaire

The quality of life questionnaire, Quality-of-Life Questionnaire for Women with Polycystic Ovary Syndrome, has been previously validated and used to examine the psychological impact of having PCOS and the effect of participation in an intervention [30, 31].

### Accelerometer

Physical activity and time sedentary will be objectively measured using the Actical™ (MiniMitter, Bend, Oregon) accelerometer, a uniaxial accelerometer that detects vertical acceleration. The Actical™ has been validated to measure physical activity in adults [32]. Accelerometers will be used at the beginning of the study to measure the participants’ usual activity (i.e., before exercise program). The Actical (28 x 27 x 10 mm/17 g) will be worn by the participants on a belt worn around the waist with the accelerometer situated at the hip, which will be demonstrated by a research assistant. Participants will be given the monitor on day 1 with data collection programed to record for 7 consecutive days, starting at 12:00 am on day 2 and ending at 12:00 am on day 8. Participants will be encouraged to wear the device on day 1 prior to start of data collection. The participants will be asked to wear the monitor at all times while awake, with the exception of water based activities such as bathing and swimming. The digitized values from the accelerometer are summed over a user-specified interval of 60 s, resulting in a count value per minute (cpm). Data will be downloaded and the raw accelerometer files visually screened for spurious data. Data will be processed using custom KineSoft software (KineSoft, Loughborough, UK). Wear time will be defined by subtracting non-wear time from 24 h. Non-wear time will be defined as at least 60 consecutive minutes of zero counts, with allowance for 1–2 min of counts between 0 and 100. Time spent in different intensities (i.e. sedentary, light, moderate and vigorous) will be calculated using published intensity thresholds for the Actical accelerometer [33, 34], which were used in the Canadian Health Measures Survey [35]. Total time in each intensity will be calculated as the sum of the minutes at a given intensity while the accelerometer is worn.

### Reproductive measures

Ovarian and uterine morphology, including the ovarian volume and the number of ovarian follicles, endometrial thickness and endometrial pattern will be assessed at the Royal University Hospital via transvaginal ultrasound using a GE Voluson® 730 Pro (Zipf, Austria). The ultrasound examination will be timed to occur during days 1-5 of participants’ menstrual cycle, with the first day of menstrual bleeding defined as day 1. Women who do not have cyclical menstrual bleeding will be seen at random times. Levels of estradiol, progesterone and an androgen index (ratio of testosterone to sex hormone binding globulin) will be assessed clinically at the Royal University Hospital and the Saskatchewan Provincial Laboratory.

### Dual-energy X-ray absorptiometry

Fat mass, lean mass, bone mineral content (BMC), bone mineral density (BMD) and hip geometry will be determined using DXA (Hologic© Discovery Wi; Bedford, MA) as previously described [35–39]. All DXA scans will be performed and analyzed by a certified radiology technologist. Whole body BMD and BMC, as well as BMD of the lumbar spine (LS) (L1–L4 vertebrae) and proximal femur regions including the femoral neck, trochanter, intertrochanteric and total hip will also be determined. DXA scans will also be used to determine geometric measures at regions of the hip [40].

### Leisure-time exercise questionnaire

Leisure-time exercise will be determined using a validated questionnaire [25]. The questionnaire will be explained to participants and examples of various levels of exercise will be provided prior to completion.

### 4-Day food record

Participants will be given an initial 4-day food record during baseline measures and will be provided with both oral and written instruction for completion. Participants will be instructed to fill out the record throughout the day as food is consumed and will be instructed on how to provide type, quantity and preparation method. Dietary intake data will be analyzed for energy and nutrient content using the dietary analysis program Food Processor (version 7, ESHA Research, Oregon). This program enables the use of both the USDA Handbook 8 (USDA, 1999) and the Canadian Nutrient File (CNF 1997 version). The database includes more than 20,000 food items, including specialty, ethnic, combination and fast foods. Other food items also can be entered from recipes.

### Glucose tolerance test

A fasted glucose tolerance test will be performed by a physician ([name]) at the Royal University Hospital. An intravenous catheter will be placed in the distal arm with a saline lock attached. Blood samples will be drawn in vacutainer tubes after discarding the saline flush from the IV catheter and the saline flush will be restored between blood sampling times. Following collection of a baseline blood sample, participants will consume a Trutol 75 g Glucose Tolerance Test Beverage (Thermo Fisher Scientific, East Providence, RI) which will be followed by blood collection every 30 min for 2 h. Blood will be collected via 6 ml EDTA or 10 ml empty collection tubes with 3 empty and 2 EDTA tubes used at baseline, 1 empty and 2 EDTA tubes used at 30, 60 and 90 min, and 2 empty and 2 EDTA tubes used at 2 h. Plasma or serum samples will be obtained by hospital staff by aliquoting samples into cryogenic vials which will be frozen at -80 °C for future analysis of insulin and glucose. Plasma samples will also be collected for assessment of other blood measures as described below. At 9-weeks, clinical blood measures will be repeated and blood collected and aliquoted as described above using 1 empty and 2 EDTA tubes. The GTT will correspond with the timing of the ultrasound examination within days 1–5 of participants’ menstrual cycle.

### Measures related to metabolic syndrome

Blood pressure, height, weight and waist circumference will be determined by a research assistant at the College of Kinesiology research facility. Weight will be measured using a calibrated scale and height determined with a standiometer. Waist circumference will be measured after removing clothing from the abdomen, by locating the top of the hip bone (iliac crest) and measuring horizontally at the tip of the landmark. Body mass index (BMI) will be determined as mass (kg) divided by height squared (m^2^). Clinical fasting bloodwork will be completed at the Royal University Hospital and include fasting plasma glucose, insulin, triglycerides, lipoproteins, C-reactive protein, vitamin D and hemoglobin A1C. Fasting bloodwork collected during the GTT or at the 9-week blood collection will be used to determine D-lactate and methylglyoxal by a technician. Liver adiposity will be assessed via ultrasonographic imaging using the ultrasound instrument GE Voluson® 730 Pro (Zipf, Austria) with analysis via Imagyne software to assess for unique echotextural characteristics [41].

### Data management and analysis

The present study will follow intent to treat analysis with measurements and analysis carried out on all participants. All identifying information will be maintained on a secure University of Saskatchewan password protected drive that is shared only with principal investigators and primary research assistants identified on our ethics submission. All hard copies of identifiable information will be securely stored in a locked filing cabinet in a locked room with restricted access. A participant coding system will be used for all data collection which will be stored separately from identifying information.

All raw data obtained will be compiled and reviewed for accuracy on an Excel Spreadsheet. Descriptive statistics will be performed for all outcome measurements for the presentation of group data as means + standard deviation as well as to identify outliers and determine normality of the data.

The treatment effect on the dependent variables will also be assessed by a group by time ANOVA (baseline, 9- and 16-weeks), with repeated measures on the time factor using Statistica (Statsoft, Chicago IL). Any missing data points at 16-weeks will be accounted for by carrying forward the 9-week value. To verify this approach, we will also run a sensitivity analysis including only participants who complete all 3 time points. Any differences determined between the groups at baseline will be used as co-variates in our analysis. Questionnaire data (Quality of Life, Pulse Consumption, Physical Activity) will be presented descriptively. The participants and group categorization will be coded such that the investigators collecting and analyzing data are blinded to which diet the participants were following.

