In women with PCOS, insulin resistance has been shown to be independent of obesity [14]. Hyperinsulinemia and adiposity exacerbate metabolic and reproductive abnormalities in women with PCOS [15–19]; therefore, our objective is to test the hypothesis that a pulse-based diet can improve symptoms related to metabolic syndrome, infertility and menstrual cycle regularity in women with PCOS. The purpose of this manuscript is to detail the study design and methodology used in a randomized clinical trial involving a diet and exercise intervention in women with PCOS.

The primary outcome measures of this study are disease measures related to PCOS including sex hormones and numbers of ovarian follicles. Secondary outcomes of this study include measures related to metabolic syndrome, quality of life, physical activity and diet.

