## Methods

### Design overview

The present study is a single-blind, parallel, stratified-randomized clinical trial. The work is funded by Saskatchewan Pulse Growers and Agriculture Agri-Food Canada. The study design is detailed in Fig. 1. The aim of the study is to determine the effect of a pulse-based diet compared to a healthy control diet on disease measures related to PCOS as well as metabolic syndrome risk factors in women with PCOS while they are enrolled in an exercise program. After the study coordinator obtains informed signed consent, study participants will be assessed to determine whether they have PCOS. Women diagnosed with PCOS will undergo baseline testing followed by a 2-week lead-in period on the healthy control diet (therapeutic lifestyle changes (TLC) recommended by the National Cholesterol Education Program). Following the lead-in, participants will repeat baseline blood measures followed by randomization to either the pulse-based diet or the TLC diet for 16-weeks while participating in an aerobic exercise program. Blood measures will be assessed after 9-weeks and at the end of the 16-week intervention, participants will undergo end of intervention testing; follow-up measures will also be assessed at 6-months and 12-months.

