**Fig. 1 Fig1:**
[figure not shown]
CONSORT flow diagram of study timeline for pulse-based diet intervention in women with polycystic ovary syndrome

The primary outcome of this study is to determine the effectiveness of a pulse-based diet compared to a healthy control diet (TLC diet) for improving PCOS disease measures including sex hormones, menstrual cycle length and, numbers of ovarian follicles. Secondary outcomes include 1) Measures of metabolic syndrome including liver adiposity; 2) Body composition; 3) Quality of life; 4) Physical Activity; and, 5) Diet.

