### Baseline measures

Prior to starting the 2-week lead-in phase and intervention, all participants will undergo baseline assessments. Assessments include a transvaginal ultrasound, fasting clinical blood measures of reproductive hormones and metabolic syndrome risk factors, glucose tolerance test (GTT) including blood sample for measurement of non-clinical metabolic syndrome risk factors, anthropometric measures, dual-energy X-ray absorptiometry (DXA), physical activity assessment via accelerometer and leisure-time activity questionnaire, 4-day food record, pulse survey questionnaire, and quality of life questionnaire.

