### Intervention

Following the 2-week lead-in phase, participants will be randomized to either the pulse-based diet or TLC diet and commence the 16-week diet and exercise intervention. The 16-week time period is based on a review of pulse-based diets for improving insulin and glucose levels [11]. In addition, the length of intervention is required to observe changes in outcome measures related to fertility. After 4-weeks of intervention, participants will meet with the study coordinator to discuss any difficulties with participating in the study and hand in the first 4-weeks of study documents which include the daily food and exercise log as well as a 1-day food record and leisure-time exercise questionnaire. After 9 weeks of the intervention, blood will be collected for clinical measures of reproductive hormones and metabolic syndrome risk factors. At the end of the 16-week intervention, baseline measures will be repeated.

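### Follicle number, a named primary outcome, has no week-9 measurement, so the stated carry-forward rule and three-occasion sensitivity analysis cannot operate for it

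*Protocol article*

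**What the plan says.** **Outcome.** The Background section states: "The primary outcome measures of this study are disease measures related to PCOS including sex hormones and numbers of ovarian follicles". The text under Fig. 1 repeats follicle number in its primary list: "improving PCOS disease measures including sex hormones, menstrual cycle length and, numbers of ovarian follicles".

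**How and when it is measured.** Under Reproductive measures, "the number of ovarian follicles, endometrial thickness and endometrial pattern will be assessed at the Royal University Hospital via transvaginal ultrasound". The scan belongs to the baseline set (Baseline measures: "Assessments include a transvaginal ultrasound, fasting clinical blood measures of reproductive hormones and metabolic syndrome risk factors"). The Intervention section has the baseline set done again at week 16. The Maintenance section lists the scan at 6 and 12 months.

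**Week 9.** Three sections describe this visit, each as blood only:
- Design overview: "Blood measures will be assessed after 9-weeks"
- Intervention: "After 9 weeks of the intervention, blood will be collected for clinical measures of reproductive hormones and metabolic syndrome risk factors"
- Glucose tolerance test: "At 9-weeks, clinical blood measures will be repeated and blood collected and aliquoted as described above using 1 empty and 2 EDTA tubes"

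**Analysis.** Data management and analysis states: "The treatment effect on the dependent variables will also be assessed by a group by time ANOVA (baseline, 9- and 16-weeks". The same paragraph fills any missing week-16 value from week 9 and limits the sensitivity analysis to women with data on all three occasions. Only questionnaire data are set apart, for descriptive reporting. The section opens by committing to intention-to-treat covering every participant.

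**The concern.** The model, the missing-data rule and the sensitivity analysis are all written around a week-9 value and apply to the dependent variables without exception. One of the named primary outcomes never has that value.

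The carry-forward is the only device the article offers for keeping women without week-16 data in the analysis. Where it cannot work, a repeated-measures ANOVA keeps only women with a complete set of values. The follicle comparison would then rest on a group selected after randomisation, and the one sensitivity analysis meant to check the missing-data handling would be empty. Otherwise the analyst must devise a model and a missing-data rule later, possibly after seeing data.

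**Working it through.** **1. Schedule against analysis, over the three occasions in the ANOVA**

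| Outcome | Baseline | Week 9 | Week 16 | Stated rules usable? |
|---|---|---|---|---|
| Sex hormones (blood) | yes | yes | yes | yes |
| Fasting glucose (blood) | yes | yes | yes | yes |
| Follicle number (ultrasound) | yes | no | yes | no |
| DXA measures | yes | no | yes | no |
| Post-load glucose tolerance values | yes | no | yes | no |

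The tubes listed for week 9 match a single draw, so fasting values exist at that visit but post-load values do not. Liver adiposity is left out because the article gives no schedule for the liver scan. Menstrual cycle length is left out because the article does not say when it is recorded.

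**2. What each rule does with follicle number**
- *ANOVA:* two of the three levels of the time factor exist. With baseline and week 16 only, the model can be fitted, and the group-by-time term is the between-group difference in change.
- *Carry-forward:* it needs a week-9 count, and none exists for any woman.
- *Sensitivity analysis:* it needs three counts per woman, and no woman has three.

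**3. The plan's own figures**

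Inputs from Sample size: mean changes of −0.18 and 0.14 mmol/L, SD 0.46, 80% power, 5% level (taken as two-sided), 32% drop-out.
- Difference: 0.14 − (−0.18) = 0.32. Effect size: 0.32 / 0.46 = 0.696, stated as 0.70 in absolute value.
- Normal approximation: n per group = 2 × (1.960 + 0.842)² / 0.696² = 32.4, so 33. The two-sample t-test gives 33.4, so 34, as stated.
- Drop-out: 34 / (1 − 0.32) = 50 per group, 100 in total, as stated.

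The sample size reproduces. It is built on fasting glucose, which is measured at week 9, so this point does not alter it.

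**4. How many women are concerned**
- Expected drop-outs: 100 × 0.32 = 32, leaving 100 − 32 = 68, or 34 per group. This assumes that every drop-out misses the week-16 scan.
- The absent week-9 scan makes a difference only for women who leave between weeks 9 and 16. Those who leave earlier would have no week-9 value even if a scan had been planned.
- If a fraction *f* of drop-outs leave after week 9, the number is 32 × *f*. The article does not give the timing of drop-out, so *f* is an assumption:

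| *f* | 0 | 0.25 | 0.5 | 0.75 | 1 |
|---|---|---|---|---|---|
| Women | 0 | 8 | 16 | 24 | 32 |

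The range is therefore 0 to about 32 of 100.

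**The case against.** The strongest reply is that an article condenses its protocol. On this view each variable is meant to be analysed at the listed occasions on which it is measured, and a two-occasion variant is detail for the full protocol or analysis plan. Part of this stands: a two-level ANOVA is an ordinary analysis, and a reader who inferred that no ANOVA could be run on follicle number would go too far. The rest does not stand. The article does not stay silent. It fixes the occasions, the imputation and the sensitivity analysis for the dependent variables in general, and two of those three cannot work for a primary outcome. If the text was meant for blood measures only, it does not say so.

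A second reply is that the article nowhere announces a completers-only analysis and in fact promises the opposite. That is correct. The exclusion of women without a week-16 scan is an inference from the stated rules, not a stated intention.

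A third reply is that 34 evaluable women per group were already planned for, so no numbers are lost against plan. This also stands. The issue is who remains in the comparison and the lack of any usable check on it.

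**Conclusion.** The point holds for follicle number, and also for DXA and post-load glucose tolerance values. As written, the carry-forward rule and the sensitivity analysis cannot operate for them, and following the text would in effect drop women without a 16-week measurement, contrary to the intention-to-treat commitment. This rests on the text alone, since Fig. 1 is not shown, but every written description of week 9 agrees.

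Three stronger readings are not supported:
- *All 32 expected drop-outs are lost because of this gap.* The 32 is total planned drop-out and only an upper bound.
- *The primary analysis as a whole shrinks to 68 women.* Sex hormones are also primary and are measured at week 9, so the stated plan works for them.
- *The trial's power or sample size is wrong on this account.* The figures reproduce and rest on fasting glucose. The article gives no basis for computing power for follicle number.

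The effect on the estimated difference in follicle number cannot be computed from the article.

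**What to change.** Amend the analysis text in three places.

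1. **Scope.** Limit the three-occasion ANOVA, the week-9 carry-forward and the three-occasion sensitivity analysis to the blood measures taken at week 9.
2. **Outcomes measured only at baseline and week 16** (follicle number, DXA, post-load glucose tolerance values). Analyse the 16-week value by ANCOVA on baseline value, diet group and Metformin stratum, in all randomised women. Only blood is repeated after the lead-in, so the baseline scan is unambiguous. Multiply impute missing 16-week values from baseline data, week-9 blood results where available, and any 6- or 12-month scan.
3. **Sensitivity analysis.** Specify one that needs no week-9 value: delta-adjusted imputation, which varies the assumed outcome in women with missing data, or at the least an analysis of women with both baseline and week-16 values.

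The imputation has limits. Early leavers have no week-9 blood, and women who leave may not return for later scans, so for some the imputation will rest mainly on baseline. That is a reason to include the delta-adjusted analysis.

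The cost is revised wording and modest extra analysis work, with no new visits, scans or participants. The article describes the study as ongoing, so the change should be made and dated before group codes are broken.

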### Sample size

A pilot study (unpublished) was carried out on preliminary data from 41 women with PCOS randomized to the pulse-based or TLC diet. Thirteen of the 41 women dropped out of the study giving a dropout rate of 32%. Changes in fasting glucose following the intervention (*n* = 28) was used to determine the required sample size for recruitment into the study. Changes in the mean fasting glucose were -0.18 and 0.14 mmol/L for the pulse-diet group and TLC group, respectively, with a population standard deviation of 0.46 and an effect size of -0.70. The pilot data provided 80% power for detecting a significant difference in fasting glucose concentration between groups (*p* < 0.05) following the intervention. It was determined 34 participants per group would be required for the study. Due to the dropout rate of 32%, the recruitment of 100 participants (i.e. 50 per group) was determined necessary.

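### The 80% power belongs to a single comparison of glucose change, but the only inferential test stated is a three-time group-by-time ANOVA, whose 2-df interaction has 72% to 84% power at 34 per group

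*Protocol article*

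**What the plan says.** The Sample size section of the protocol article works from pilot data on one change score per woman: "Changes in the mean fasting glucose were -0.18 and 0.14 mmol/L for the pulse-diet group and TLC group, respectively". The spread and the standardised difference are reported as "population standard deviation of 0.46 and an effect size of -0.70". It concludes "It was determined 34 participants per group would be required for the study" and inflates this for dropout: "Due to the dropout rate of 32%, the recruitment of 100 participants (i.e. 50 per group) was determined necessary". The power statement is "80% power for detecting a significant difference in fasting glucose concentration between groups (*p* < 0.05) following the intervention". The section mentions neither the 9-week visit nor any correlation between visits.

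Data management and analysis says the treatment effect on the dependent variables will be assessed by a "group by time ANOVA (baseline, 9- and 16-weeks), with repeated measures on the time factor". The sentence says this is done in addition to what precedes it, but only descriptive statistics precede it. No other inferential test of the treatment effect is described, and no single contrast is named as deciding. The analysis is by intention to treat on all participants. A missing 16-week value is replaced by the 9-week value, and women with all three time points form a sensitivity analysis.

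Design overview and Intervention list blood measures at 9 weeks. They do not list the ultrasound at that visit.

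**The concern.** The trial is sized for one test and analysed with another. The sizing test asks whether the two diets differ in change from before to after the intervention. The interaction over three times asks whether the two mean profiles differ in shape anywhere. Two things are at stake.

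- **Power.** The 80% was not derived for the interaction, whose power depends on inputs the article does not give: how much of the effect is present at week 9, and how the three measurements covary.
- **Interpretation.** A significant interaction does not by itself say that the diets differ at the end of the 16-week intervention, which is what the trial sets out to learn. This reaches beyond glucose. Sex hormones, among the primary outcomes, are also blood measures taken at 9 weeks.

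**Working it through.** **Inputs from the Sample size section.** Mean changes -0.18 and 0.14 mmol/L, so the difference is 0.32. SD 0.46, read here as the SD of change. 34 per group; dropout 32%; p < 0.05, taken as two-sided.

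**Assumed, because the article does not give them.** Compound symmetry of the three measurements, and the between-diet difference at week 9, written δ9.

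**Step 1. Reproduce the plan's figure.**
- Effect size: 0.32/0.46 = 0.696, stated as 0.70 in absolute value.
- Two-sample t-test, 34 per group, two-sided 5%: power 80.7%. With 33 per group it falls just below 80%, so 34 reproduces. A one-sided test would need only 26 (normal approximation), which supports the two-sided reading.
- Dropout: 34/(1 - 0.32) = 50 per group, 100 in total.

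**Step 2. Power of the stated interaction at 34 per group.**
- Degrees of freedom: (2 - 1)(3 - 1) = 2 for the interaction; 2 × (2 × 34 - 2) = 132 for error.
- Under compound symmetry the variance of a change is 2σ²(1 - ρ) = 0.46², so σ²(1 - ρ) = 0.2116/2 = 0.1058.
- Noncentrality: λ = (34/2) × Σ(δt - mean δ)² / 0.1058, with δ = (0, δ9, 0.32).
- Example, δ9 = 0.16: the mean is 0.16, Σ = 0.0256 + 0 + 0.0256 = 0.0512, and λ = 17 × 0.0512/0.1058 = 8.23.

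| Share of effect at week 9 | δ9 | λ | Power, F(2,132) |
|---|---|---|---|
| none | 0 | 10.97 | 84.3% |
| one quarter | 0.08 | 8.91 | 75.6% |
| half | 0.16 | 8.23 | 72.0% |
| linear in weeks (9/16) | 0.18 | 8.27 | 72.2% |
| three quarters | 0.24 | 8.91 | 75.6% |
| all | 0.32 | 10.97 | 84.3% |

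Simulation of the repeated-measures ANOVA (20,000 runs) gives 72.0% to 72.1% for the half and linear rows.

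**Step 3. What the interaction responds to.** Take a difference present only at week 9, δ = (0, 0.32, 0). Then Σ(δt - mean δ)² = 0.0683, λ = 10.97 and power is 84.3%. This equals the power for an effect complete by week 9 and sustained to week 16, so the test cannot tell the two apart.

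**Step 4. The plan's all-participants analysis.** Simulated with 50 per group, of whom 0.32 × 50 = 16 have week 9 carried forward, assuming every dropout has a week-9 value:
- half the effect at week 9: about 77%
- linear in weeks: about 80%
- three quarters: 87% to 88%
- all: about 96%

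**Step 5. A baseline-adjusted 16-week contrast at 34 per group.** Relative to the change score, the variance is multiplied by σ²(1 - ρ²)/[2σ²(1 - ρ)] = (1 + ρ)/2.
- ρ = 0.7: ratio 0.85, effect size 0.696/√0.85 = 0.755, power about 87%.
- ρ = 0.4: ratio 0.70, effect size 0.696/√0.70 = 0.831, power about 92%.

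The correlations are assumed.

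**The case against.** **The low figure is the bottom of a curve.** A reader might infer that the trial has 72% power. The documents do not support that. Half the effect at week 9 is the minimum under compound symmetry, and neither the week-9 effect nor the covariance is given. This stands: the result is a range that straddles 80%.

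**The analysed number is not 34.** The main analysis includes all participants, with week 9 carried forward. This also stands. If every dropout has a week-9 value, the shortfall is about 3 points at half the effect and is gone at three quarters or more. It does not remove the issue, for two reasons. The article does not say how many dropouts will have a week-9 value. Carrying forward also dilutes a late effect: the expected 16-week difference becomes 0.68 × 0.32 + 0.32 × δ9, which is 0.243 at δ9 = 0.08. In addition, the Sample size section counts on 34 per group after dropout, and the completers' analysis returns to about that number.

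**The article does not say that the omnibus interaction decides.** A 16-week comparison may be specified in an analysis plan that is not shown. A reader should therefore not infer that no 16-week comparison will be made. What stands is narrower: the analysis that is stated differs from the one that was powered. Reading the ANOVA as a group main effect would not close the gap, because averaging in the baseline visit dilutes the effect. At an assumed correlation of 0.5, that test has 41% power (half the effect at week 9) to 64% (all of it).

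**The reach is limited.** With only baseline and 16 weeks, the interaction has 1 degree of freedom and is the t-test on change. Follicle counts are therefore untouched. The power figures concern fasting glucose, which the article places among its secondary measures. Both points stand.

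**Conclusion.** The mismatch is real and the size of its effect on power is moderate and conditional. The 34 per group reproduces only as a two-sample comparison of change (80.7%, if 0.46 is the SD of change). For blood measures the stated ANOVA interaction is a 2-df test with 72% to 84% power at 34 per group under assumed compound symmetry. Under the carry-forward analysis of 50 per group it has about 77% at half the effect and more than 80% at three quarters or above. The documents do not support calling the trial underpowered as such.

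The interpretive problem does not depend on where power falls. A significant interaction would not show that the diets differ at 16 weeks, and the test is as sensitive to a vanished 9-week difference as to an early, sustained one. Because the remedy costs almost nothing, the change should be made.

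**What to change.** 1. In Data management and analysis, declare the between-diet contrast at 16 weeks, adjusted for the outcome's baseline value and Metformin stratum, as the test of the treatment effect. Report the 9-week contrast and the group-by-time interaction as supportive.
2. In Sample size, state that 34 per group was derived for an unadjusted comparison of baseline-to-16-week change (about 80% power, with 0.46 as the SD of change). Add that it is conservative for the adjusted contrast: about 87% to 92% for an assumed baseline-to-16-week correlation of 0.7 down to 0.4. Do not attach the 80% to the adjusted contrast, since that would again pair a power figure with a different test.

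The cost is wording in two sections. Baseline values and Metformin use are already collected, and no visits or participants are added. Keeping the interaction as the deciding test would be dearer: under gradual build-up with compound symmetry it needs 41 evaluable per group, or 41/0.68 = 60.3, so 61 recruited per group and 122 in total against the planned 100. The study is described as ongoing, so the contrast should be fixed before results by diet are seen.
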